### Data collection and analysis

All data will be provided by the AOK. Data of the DMP groups are retrieved by the DMP documentation forms which have to be completed routinely every 3 to 6 months during the scheduled DMP visits of participating patients. The information about the tracer medication identifying patients of the control group is also provided by the AOK. The data reporting will follow the CONSORT recommendations for cluster randomized trials [16].

Data analysis will be performed according to the intention-to-treat (ITT) method. For missing data the 'last observation carried forward' -method will be used.

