#### Outcome-parameter

Outcome parameters were defined considering best available evidence, legal regulations and feasibility. According to our two scientific hypotheses two groups of outcome parameters were defined: "outcome parameters I" for the comparison of the DMP groups and "outcome parameters II" for the comparison of DMP and routine care. This differentiation of the outcome parameters is essential because in the control group availability of patient data will be limited to process indicators only. The outcome parameters are displayed in Table 1.

**Table 1 T1:** Primary and secondary outcome parameters

**OUTCOME PARAMETERS I**	**OUTCOME PARAMETERS II**
**DMP 1 vs. DMP 2**	**DMP 1 vs. CG**
***Primary outcome parameter***	***Primary outcome parameter***

Proportion of patients achieving target values for HbA1c and RR according to the legal regulations (10)	Proportion of patients with prescriptions for antidiabetic, antihypertensive and lipid-lowering drugs

***Secondary outcome parameters***	***Secondary outcome parameters***

Proportion of patients with prescriptions for antidiabetic, antihypertensive and lipid-lowering drugs	----
Proportion of patients with referrals to ophthalmologists, specialists for diabetology and diabetic feet	Proportion of patients with referrals to ophthalmologists, specialists for diabetology and diabetic feet
Proportion of patients referred to a patient education training for diabetes and hypertension	Proportion of patients referred to a patient education training for diabetes and hypertension
Proportion of patients with severe complications (amputation, dialysis etc.)	Proportion of patients with severe complications (amputation, dialysis etc.)
Proportion of patients with > 2 hospitalizations in the last 6 months	Proportion of patients with > 2 hospitalizations in the last 6 months
Consultation rate	Consultation rate
Days of incapacity to work	Days of incapacity to work
Mean differences of HbA1c, RR, BMI and glomerular filtration rate	---
SCORE risk chart (RR, cholesterol, smoking status, age, gender)	---
Drop out rate from the DMP	---

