### Intervention

The minimum requirements for the Diabetes-DMP are regulated by law and defined in the RSAV [10]. According to the legal regulations the intervention in the DMP1 group comprises consultations at 3- or 6-months intervals. During these consultations a detailed diabetes-specific anamnesis and physical examination incl. taking blood pressure and an analysis of HbA1c are carried out. Furthermore agreements are made concerning further treatment, e.g. target values for HbA1c and blood pressure and participation on patient education programs for diabetes or hypertension. All medical findings as well as the current medication have to be documented within structured, standardized documentation sheets at each consultation. If required a referral to a specialist (e.g. ophthalmologist) will be arranged. Furthermore the GPs get a special diabetes-handbook including current, evidence-based information about diabetes therapy. The GPs participating in the DMP1 group will receive no additional intervention.

There are major difficulties introducing new evidence into general practice requiring comprehensive implementation support at different levels (patients, doctors, practice team) [17,18]. Therefore, in the DMP 2 group implementation support at the level of doctors and practice team will be provided. In addition to the clinical interventions at patients level in the DMP group 1 several components aiming at optimizing the implementation process are provided in this group (= implementation interventions) (Table 2).

**Table 2 T2:** Implementation Interventions in DMP 2 group

**Interventions**	**Description**
Interactive quality circle meetings	During these meetings all aspects of evidence based treatment of diabetes in a primary care setting will be discussed (2 × per year).
Educational meetings for medical assistants	During these meetings medical assistants will be supported in finding individual strategies for optimal implementation of the DMP in their practices (2 × per year).
Outreach visits	During these meetings individual problems within the implementation process of the DMP will be discussed with the GP and the assistant team (1 × per year)
Homepage with "best practice" examples	Detailed information for the praxis team about Diabetes-DMP incl. case studies via internet (electronic individual feedback)

The control group represents routine care without DMP. There will be no intervention at all.

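### DMP 1 vs DMP 2: outcome data come from forms that belong to the programme, and only DMP 2 gets help implementing it, so recording may differ between the randomised arms

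*Protocol article*

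**What the plan says.** Under Data collection and analysis, the protocol article first names the provider, "All data will be provided by the AOK", and then the source for both randomised arms: "Data of the DMP groups are retrieved by the DMP documentation forms which have to be completed routinely every 3 to 6 months". No second source is named for DMP 1 or DMP 2.

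Under Intervention, documentation is described as part of the DMP that both arms receive: "All medical findings as well as the current medication have to be documented within structured, standardized documentation sheets at each consultation". The arms differ in implementation support. For DMP 1 the text says "The GPs participating in the DMP1 group will receive no additional intervention". DMP 2 adds quality circles, yearly outreach visits, a homepage with electronic feedback, and meetings at which "medical assistants will be supported in finding individual strategies for optimal implementation of the DMP in their practices".

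Table 1 lists as a secondary outcome for DMP 1 vs DMP 2 "Proportion of patients with prescriptions for antidiabetic, antihypertensive and lipid-lowering drugs". It also lists specialist referrals, patient education referrals, severe complications, hospitalisations, consultation rate and incapacity days. All of these appear in the DMP 1 vs control column as well, where prescriptions are the primary outcome.

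**The concern.** The measuring instrument is a component of the programme, and one randomised arm is helped to run that programme better. If the help makes forms more complete, recorded outcomes can differ between arms when care does not. Randomisation gives no protection, because the difference arises after allocation.

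The outcomes most exposed are proportions of patients with a recorded event, where an item left off the form may count as not done. A DMP 2 advantage in prescriptions or referrals could then not be separated from a documentation effect, and the error would favour the second hypothesis (DMP 2 more effective than DMP 1). For adverse outcomes the same mechanism could hide a real benefit.

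**Working it through.** **Which way the bias would run.** Suppose recording is fuller in DMP 2 and care is equal.

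- Prescriptions and referrals: the recorded proportion rises, and DMP 2 looks better.
- Severe complications, hospitalisations, incapacity days: the recorded figure rises, and DMP 2 looks worse.
- Consultation rate: the recorded rate rises, with no clear good or bad direction.
- HbA1c and blood pressure targets (primary): these also come from the forms. Any effect would run through missing forms and last observation carried forward, and has no fixed direction.

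**Effective sample size.** Inputs from the protocol: 100 GPs per arm, 20 patients per GP, ICC 0.05. The article gives no alpha, power or target difference, so its 200 GPs cannot be recalculated. This point does not depend on that figure.

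- Patients per arm: 100 × 20 = 2000
- Design effect: 1 + (20 − 1) × 0.05 = 1.95
- Effective patients per arm: 2000 / 1.95 ≈ 1026

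**Size of a pure recording effect.** Let the true rate p be equal in both arms, and let forms capture a share s1 in DMP 1 and s2 in DMP 2. The recorded rates are a = p·s1 and b = p·s2. Then SE = √[(a(1−a) + b(1−b)) / 1026], z = (b − a)/SE, and the chance of a two-sided p < 0.05 is about Φ(z − 1.96). Every p and s is an assumption, since the protocol gives none.

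- p = 60%, capture 80% vs 85%: 48% vs 51%. SE = √[(0.2496 + 0.2499)/1026] = 0.0221, z = 0.03/0.0221 ≈ 1.4, chance of significance about 27%.
- p = 60%, capture 80% vs 90%: 48% vs 54%. SE = √[(0.2496 + 0.2484)/1026] = 0.0220, z = 0.06/0.0220 ≈ 2.7, chance about 78%.

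Other assumed values with the same formula:

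| True rate | Capture DMP 1 vs DMP 2 | Recorded | False difference (points) | Chance of p < 0.05 |
|---|---|---|---|---|
| 70% | 90% vs 95% | 63.0% vs 66.5% | 3.5 | 38% |
| 70% | 85% vs 95% | 59.5% vs 66.5% | 7.0 | 91% |
| 30% | 85% vs 95% | 25.5% vs 28.5% | 3.0 | 33% |
| 5% (complications) | 80% vs 95% | 4.0% vs 4.75% | 0.75, against DMP 2 | 13% |

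**Against what the trial can detect.** At 80% power the detectable difference near 50% is about (1.96 + 0.84) × 0.022 ≈ 6 points. Over base rates of 30–70%, power of 80–90% and drop-out of 0–20% (all assumed) it is roughly 6 to 8 points. A 10-point capture gap in a common outcome reaches that size. A 2-point gap gives at most 2 points.

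**Effect of drop-out.** The 2000 per arm ignores losses. If 20% of practices were lost (assumed), the effective number is 0.8 × 1026 ≈ 820, and each z falls by the factor √0.8 ≈ 0.89: 2.7 becomes about 2.4, and 1.4 becomes about 1.2.

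**Whether another source exists.** Control patients come from practices outside the DMP, so they have no DMP forms. Table 1 nevertheless plans prescriptions, referrals, complications, hospitalisations, consultations and incapacity days for DMP 1 vs control. These must come from a non-form source, and the AOK supplies all data. The DMP patients are AOK-insured too.

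**The case against.** A reader might infer that DMP 2 trains practices to fill in forms. The text does not say so. Table 2 names evidence-based treatment, implementation strategies, implementation problems and case material with feedback; documentation is not mentioned, and the forms are compulsory and standardised in both arms. The completeness gap could be small. This stands, and the mechanism is therefore plausible but not documented.

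A reader might also infer that every secondary outcome is biased towards DMP 2, or that the primary outcome is. The first fails because fuller recording of adverse outcomes counts against DMP 2. The second fails because no direction can be shown for the HbA1c and blood pressure targets.

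Nor does the number of forms differ by design. A 24-month period gives about 4 forms at 6-month intervals (24/6) or 8 at 3-month intervals (24/3), but both arms share these intervals, and the article states no rule that counts an event on any form in the period.

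The strongest objection concerns the source. The article does not map outcomes to sources, the AOK provides everything, and an article may leave such mapping to the full protocol. The sponsor may already intend to use non-form data in the DMP arms. The description of the sheets names findings and medication but not referrals, so it is only the general sentence that places referrals on the forms. That sentence is nevertheless unqualified: as written, data of the DMP groups come from the forms. If something else is meant, the sentence should be corrected.

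**Conclusion.** The point holds in limited form. As written, both randomised arms are measured by forms that belong to the programme, and only one arm is supported in implementing it. Differential recording is a real risk for the secondary outcomes, favouring DMP 2 for prescriptions and referrals and working against it for complications, hospitalisations and incapacity days.

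The size cannot be stated. With a 60% true rate it runs from a false 3 points (z about 1.4) for a 5-point capture gap to a false 6 points (z about 2.7) for a 10-point gap. This rests on assumed capture rates, on unrecorded items counting as absent, on the ICC of 0.05 and on full recruitment without losses. The change is worth making because it is cheap and most of the alternative data must be obtained for the control comparison anyway.

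**What to change.** For DMP 1 vs DMP 2, take prescriptions, severe complications, hospitalisations, consultations and incapacity days from the same AOK non-form source that must supply them for the control group. Do the same for referrals where AOK data hold them. Amend the data collection section to say so. Keep the forms for HbA1c, blood pressure and other clinical values.

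For outcomes available only on forms, report the number of forms per patient and item completeness by arm, and interpret differences between arms in that light. This describes the problem but does not remove it.

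The cost is a wider AOK extract and some delay in data delivery. If the sponsor already plans this, only the wording changes.

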### Timeframe of the study

The study team will start to invite GPs at the end of September 2005. After receiving a written declaration of their willingness to participate in the study and to accept random assignment to the different groups GPs will be randomized.

Patient inclusion and pre-data collection will start in 2005. The observation period will be 24 months.

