### Ethical principles and vote of the ethics committee

The study is being conducted in accordance with medical professional codex and the Helsinki Declaration as of 1996 as well as the German Federal Data Security Law (BDSG). DMP participation of patients is voluntary and can be cancelled at any time without provision of reasons and without negative consequences for their future medical care.

The study protocol was approved by the ethics committee of the University of Heidelberg in April 2005 (Approval-Nr. 098-2005). Furthermore the evaluation of the DMP is regulated by law in the Fifth Book of Social Code (§137 f. Abs. 4 SGB V).

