## Discussion

There are specific difficulties in evaluating the effectiveness of complex interventions such as disease management programs [19], particularly, in our case that implementation process has already started [15]. At the moment it is not conceivable to which phase of the implementation process the DMP actually has preceded. However, the DMP group 2 represents an ideal implementation of the DMP within the scope of the German law regulation.

To adapt the evaluation design to the real conditions of diabetes care in Germany at the moment, but also to consider the ongoing implementation process we have chosen the design of a prospective randomized-controlled comparison of the two DMP groups embedded in the quasi-experimental design of a controlled before-after study with a blinded control group. The quasi-experimental design is predetermined because allocation to the control group can not be perfomed randomly and because baseline values for patients participating in the DMP have not been documented.

A fully experimental design with a randomized control group was rejected by the authors, because this could create an artificial care situation. That is informing patients and GPs of the control group about the study and probably asking for completing any questionnaires would introduce an enormous bias.

According to the theoretical model for design and evaluation of complex interventions by Campbell et al the presented study can be assigned to phase III and IV (15, 20). However, pilot projects have shown that an observation period of 24 months will be too short to show significant differences in severe clinical endpoints (i.e. amputations, diabetic renal insufficiency, cardio-vascular events). Therefore it was decided to have a combination of HbA1c and blood pressure as primary endpoint in the randomized part of the trail and prescriptions in the quasi-experimental part of the trial.

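### Last observation carried forward can bias the randomised DMP 1 vs DMP 2 comparison in either direction, because HbA1c and blood pressure recording stops when a patient leaves the programme

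*Protocol article*

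**What the plan says.** All of the following is in the protocol article.

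- *Data collection and analysis* fixes both the analysis principle and the handling of gaps: "Data analysis will be performed according to the intention-to-treat (ITT) method", and "For missing data the 'last observation carried forward' -method will be used".
- The same section takes the DMP-group data from documentation forms that are "completed routinely every 3 to 6 months during the scheduled DMP visits of participating patients".
- *Outcome-parameter*, Table 1, makes the share of patients at target for HbA1c and blood pressure the primary outcome for DMP 1 vs DMP 2. It lists "Drop out rate from the DMP" as a secondary outcome of the same comparison.
- *Ethical principles and vote of the ethics committee*: "DMP participation of patients is voluntary and can be cancelled at any time without provision of reasons".
- *Timeframe of the study*: "The observation period will be 24 months".

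**The concern.** The primary outcome of the randomised comparison is observed only while a patient attends DMP visits. Once the patient leaves, no further HbA1c or blood pressure value reaches the study. LOCF then assumes that target status stayed as it was on the last form, and the analysis handles that status as a measurement.

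Two things are at stake. First, if control changes after exit, each arm's proportion is shifted by an amount that depends on how many patients left and how far they changed. The arm difference is free of bias only if these shifts are equal. Drop-out from the DMP is to be compared between the same two arms, so the plan itself leaves open that it may differ. Second, entering a filled-in value as observed ignores the uncertainty about what it should have been. Labelling the analysis intention-to-treat keeps the leavers in the denominator but does not repair either problem.

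**Working it through.** **Inputs from the article.** ICC 0.05; 200 GPs with 20 patients each; 100 GPs per DMP group, hence 2000 patients per arm; 24 months of observation; forms every 3 to 6 months.

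**Inputs that are assumed.** Drop-out share, change in attainment after exit, target attainment (40% or 50%), two-sided alpha 5% and power 80%. The article gives none of these.

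**Age of a carried value.** If the last form is the first follow-up form, the value is carried for 24 − 6 = 18 to 24 − 3 = 21 months. If only a form from inclusion exists, it is carried for the whole period. If only the last scheduled form is missing, it is carried for about one interval of 3 to 6 months.

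**The design's own resolution.**
- Design effect = 1 + (20 − 1) × 0.05 = 1.95.
- Effective sample size = 2000 / 1.95 ≈ 1026 per arm.
- Detectable difference at 50% attainment = 2.80 × √(2 × 0.25 / 1025.6) = 0.062, or about 6.2 points.

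The 200 GPs cannot be reproduced as such, because the inputs are not given. They can be back-solved: at 40% attainment and 80% power, a difference of 6.15 points needs about 198 GPs with no allowance for drop-out. With 80 of 100 GPs per arm remaining, the detectable difference rises to about 6.9 points.

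**LOCF bias.**
- Bias in one arm = drop-out share × (attainment at the carried form − true attainment at the end of observation), among leavers.
- Bias in the difference (DMP 2 − DMP 1) = DMP 2 term − DMP 1 term.

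| Drop-out DMP 1 / DMP 2 | Change after exit (points) | Bias DMP 1 | Bias DMP 2 | Bias in difference |
|---|---|---|---|---|
| 20% / 10% | −20 | +4 | +2 | −2 |
| 20% / 10% | −10 | +2 | +1 | −1 |
| 20% / 10% | +10 | −2 | −1 | +1 |
| 20% / 10% | +20 | −4 | −2 | +2 |
| 10% / 20% | −20 | +2 | +4 | +2 |
| 10% / 20% | +20 | −2 | −4 | −2 |
| 20% / 20% | −20 | +4 | +4 | 0 |

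The sign turns on two unknowns: which arm loses more patients, and whether leavers get better or worse. With equal shares and equal change, the bias in the difference is zero, although each arm's proportion is still wrong.

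**What a bias of this size does.** At 40% attainment in both arms, SE = √(2 × 0.4 × 0.6 / 1025.6) = 0.0216. With no true effect, the chance of a significant result is 1 − Φ(1.96 − b/SE) + Φ(−1.96 − b/SE). For b = 1 point this is about 7.5%, and for b = 2 points about 15.2%, against a nominal 5%.

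**The case against.** Several objections carry weight.

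- **Unequal drop-out is not established.** A reader might infer from Table 1 that drop-out is expected to differ between the arms. The table only lists the drop-out rate as an outcome, with no figure and no direction. What stands is that it may differ.
- **No direction can be claimed.** It is tempting to say that LOCF hides the benefit of DMP 2 if DMP 2 retains patients better. That holds only if leavers worsen after exit, and by a similar amount in both arms. The article says nothing on this, and if leavers improve the sign reverses.
- **Early leavers are not shown to lack a value to carry.** The *Discussion* says that "baseline values for patients participating in the DMP have not been documented", and a reader might take this to mean that a patient who leaves at once has no earlier form. The remark explains why the comparison with routine care is quasi-experimental. *Selection of participants* enrols patients already in the DMP, and *Timeframe of the study* plans data collection beforehand, so earlier forms probably exist.
- **The time point is inferred.** Table 1 names none for the primary outcome. The end of the observation period is the natural reading, but still a reading. The lag of 18 to 21 months is also an extreme case.
- **A condensed article may leave sensitivity analyses to the analysis plan.** Agreed; their absence is not criticised here. The choice of LOCF is different, because the article states it.
- **The alternatives also make assumptions.** Agreed. A mixed model and multiple imputation rely on missing at random, which is doubtful if exit depends on unrecorded control. A logistic mixed model also gives a patient-specific odds ratio, whereas the outcome is a proportion. AOK claims are not shown to hold HbA1c or blood pressure; *Outcome-parameter* limits the data available for the control group to process indicators. The fix has to deal with each of these.

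None of this supports LOCF as the primary method.

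**Conclusion.** The point holds as a criticism of a stated method. In the randomised comparison, LOCF can bias the difference in target attainment in either direction, and it treats filled-in values as observed. The article supplies no drop-out or attainment rates, so neither the size nor the sign of the bias can be derived from it.

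Under assumed drop-out of 20% in one arm and 10% in the other, and a post-exit change of 10 to 20 points either way, the bias in the difference is 1 to 2 points. Set against a detectable difference of about 6.2 points, that is not negligible. If drop-out share times post-exit change is equal in both arms, it vanishes.

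The point concerns DMP 1 vs DMP 2. The primary outcome against routine care is prescriptions, and it does not depend on HbA1c or blood pressure values.

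**What to change.** For the randomised comparison, replace LOCF as the primary method by one of two approaches:

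- a mixed-effects logistic model on all documented forms, with random effects for practice and patient and a time-by-arm term, standardised to a difference in proportions at the end of the observation period; or
- multilevel multiple imputation that respects the practices and uses the repeated forms, pre-intervention forms where available, and AOK claims as auxiliary predictors only.

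Name the end of the observation period as the time point of the estimate. State that both approaches rely on missing at random. Add sensitivity analyses that depart from it: leavers counted as not at target, or a delta adjustment over a stated range. LOCF can stay as a further sensitivity analysis.

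The repeated forms are already collected, so no new data are needed. The cost is a change of wording, some programming, a more complex model to explain, and somewhat wider intervals.
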